**Methods:**

This acute randomized crossover trial will recruit healthy adults (n = 106) in East London between November 2023 and March 2025. Two test drinks are consumed by participants (a glucose drink containing 75 g glucose and pure orange juice) on different occasions. PGRs are monitored before and after drinking every 30 min for up to 2 h via finger prick. A fasting blood sample obtained via phlebotomy will be used for plasma 25(OH)D and relevant tests. A knowledge/perception questionnaire about vitD and a 4-day food diary (analyzing vitD dietary intake) will also be collected. Data will be analyzed using a multiple linear regression model adjusted by confounding factors (age, gender, body mass index, and body fat percentage).

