## Introduction

Health patterns differ significantly between ethnic minority groups and the White population. In the UK, the risk of developing type 2 diabetes mellitus (T2DM) is 3–6 times greater in South Asians (SAs) and up to three times greater in Black African-Caribbeans (ACs) than in White Caucasians, and people in these groups develop this condition at a younger age (Meeks et al., 2016). East London is among the areas with the highest proportion of ethnic minority groups (Gov.uk, 2022a) and the highest prevalence of T2DM (Diabetes, 2021). Although multiple factors, including socioeconomic standing, diet, culture and attitudes, language barriers, genetics, and lifestyles, have been identified (Hanif and Susarla, 2018), research into biological diversity is scarce. Recent research revealed that the postprandial glucose peak in SAs is 2–3 times greater than in White Caucasians after identical carbohydrate loads are reached (Tan et al., 2017). Although obesity is believed to account for 90% of the risk of developing T2DM due to obesity causing insulin resistance (Grant et al., 2021) and some ethnic minority groups, e.g. Black people, have a higher prevalence of overweight and obesity than White British people do (73.6% vs. 63.3%) (Gov.uk, 2020), other biological mechanisms, including vitamin D (vitD) deficiency, are poorly understood.

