VitD deficiency in ethnic minorities in the UK is well known and is described as an unrecognized epidemic (Darling, 2020). In the UK, 50% of SAs and 33% of Black ACs demonstrate vitD deficiency, whereas 17.5% of White Caucasians do (Sutherland et al., 2021), which is primarily due to more subcutaneous pigmentation that absorbs ultraviolet B from sunlight and reduces vitD production in the skin and at high latitudes in the UK (Yousef et al., 2023). This situation is worse in East London. In Tower Hamlets, a borough of East London, 80–97% of the residents are thought to have vitD deficiency, significantly higher than the national population at 50% (Towerhamlets.gov.uk, 2017). An inverse association of serum 25(OH)D levels with insulin resistance was observed in healthy adults (Yin et al., 2022) and diabetic patients (Abubaker et al., 2022). Recent evidence from systematic reviews and meta-analyses of randomized controlled trials (RCTs) suggests that vitD supplementation may help reduce fasting plasma glucose concentrations, HbA1c levels, and insulin resistance in patients with T2DM (Afraie et al., 2024; Farahmand et al., 2023). However, little evidence is available that focuses on ethnic minority groups or residents in East London, indicating that AC and SA communities are underrepresented in the evidence base concerning diabetes and vitD.

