## Outcome measures

The primary outcome will be the association of plasma 25(OH)D with the PGRs represented as the incremental areas under the curve (iAUCs) and peak values (PVs) in different ethnic groups. The secondary outcomes include the difference in iAUCs, PVs, and the following variables relating to vitD status between ethnic groups. C-reactive protein (CRP) is reported to have an inverse relationship with 25(OH)D, indicating an anti-inflammatory property of vitD (de Oliveira et al., 2017). The total cholesterol and high-density lipoprotein (HDL) have inverse and positive associations, respectively, with vitD status (Alkhatatbeh et al., 2019). BMI and body fat percentage are used as confounding factors of 25(OH)D (Grønborg et al., 2015) and PGRs to drinks (Dhaheri et al., 2010). PTH and calcium are closely related to vitD metabolism (Goltzman et al., 2018). The plasma 25(OH)D and PTH are measured using an AIA-900 immunoassay analyzer (Tosoh Bioscience, USA); CRP, calcium, total cholesterol, and HDL are measured using Horiba Pentra 400 Biochemistry Analyzer (Horiba, Japan). The body weight and fat percentage are measured with dual-frequency bioelectrical impedance analysis technology by TANITA DC-360 P (Tanita, Amsterdam) and body height by stadiometer. Dietary vitD intake will be analyzed by a 4-day estimated food diary analyzed using Nutritics software (Nutritics Ltd, Dublin). Knowledge and perception of vitD will be assessed by an online questionnaire (Appendix 2) collected via Qualtrics survey platform (Qualtrics, Provo, UT).

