## Data analysis

The sample size was calculated using G*Power software (version 3.1.9.7; Heinrich Heine University, Düsseldorf, Germany), based on F-tests for ANOVA: repeated measures, between-subjects factors. This study aims to achieve an effect size of 0.25 in the PGRs among three ethnic groups, considering that the response is taken from five different time points with 30-min intervals for each person, and to achieve 80% power in the study, we will need 32 people in each group (n = 96 in total) at the 5% level of significance. The details of the sample size calculation can be found in Appendix 3. Considering the acute nature of the study, we believe 10% of the attention is sufficient; therefore, the target number of recruitments is 106 participants. Data normality will be assessed using the Kolmogorov–Smirnov test. Continuous variables with a normal distribution will be presented as means ± standard deviations, while non-normally distributed data will be reported as medians and interquartile ranges. Categorical data are presented as numbers and percentages. The iAUC is calculated using approximated trapezoidal numerical integration (Chlup et al., 2008), and only the incremental area above the fasting level will be included. The association of plasma 25(OH)D concentrations and the iAUCs and PVs, respectively, will be analyzed using a multiple linear regression model adjusted by age, gender (using dummy variables), BMI, and body fat percentages, including all participants, as well as in different ethnic groups. The iAUCs and PVs concentrations between ethnic groups after each drink consumption will be analyzed by one-way ANCOVA adjusted by confounding factors including fasting glucose concentration, age, sex, BMI, and body fat percentage. The correlation of iAUCs and PVs between the two drink consumptions is analyzed by Pearson's correlation to identify the difference in the pattern of PGRs to different drink consumptions. Other continuous variables (e.g. plasma 25(OH)D etc.) between ethnic groups will be analyzed by one-way ANCOVA adjusting confounding factors (age, gender, BMI and body fat percentage). Categorical variables, e.g. gender, the percentage of patients with vitD deficiency etc., are compared between ethnic groups via Chi-square tests. The statistical significance will be reported with a *P*-value (significance was set at *P* ≤ 0.05, two-tailed) and a 95% confidence interval. The statistical software IBM SPSS 29 will be used to analyze the data. The percentage of missing data is expected to be low based on our previous experience. Therefore, regression imputation is used to address missing data. Both intention-to-treat analysis and per-protocol analysis will be used for the data analysis.

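### The all-participant regression of glycemic response on 25(OH)D leaves out ethnicity, so ethnic differences can show up as a vitamin D association in that pooled fit

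*Protocol article*

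**What the plan says.** The Outcome measures section states: "The primary outcome will be the association of plasma 25(OH)D with the PGRs represented as the incremental areas under the curve (iAUCs) and peak values". It adds that this is to be examined across the ethnic groups.

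The Data analysis section gives the model: a multiple linear regression of iAUC and of peak value on 25(OH)D, "adjusted by age, gender (using dummy variables), BMI, and body fat percentages, including all participants, as well as in different ethnic groups". The Methods part of the abstract names the same covariates: "multiple linear regression model adjusted by confounding factors (age, gender, body mass index, and body fat percentage". Both lists are closed, and neither contains ethnicity. Ethnicity enters only as the group factor of separate ANCOVAs and Chi-square tests, and as the variable that defines the within-group regressions.

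The Introduction ties ethnicity to the exposure: "50% of SAs and 33% of Black ACs demonstrate vitD deficiency, whereas 17.5% of White Caucasians do". It also ties ethnicity to the outcome, reporting that "the postprandial glucose peak in SAs is 2–3 times greater than in White Caucasians after identical carbohydrate loads". It lists routes from ethnicity to diabetes risk other than vitamin D: "multiple factors, including socioeconomic standing, diet, culture and attitudes, language barriers, genetics, and lifestyles, have been identified". The sample size is set to detect an ethnic difference in glycemic response of f = 0.25.

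**The concern.** The sample is recruited as three ethnic groups that, on the protocol's own account, differ in 25(OH)D and are expected to differ in glycemic response. A variable related to both exposure and outcome, and preceding both, confounds a regression that omits it. The pooled 25(OH)D slope then blends two things: the association among people of the same ethnicity, and the contrast between groups with low and high average 25(OH)D.

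The study is meant to separate a vitamin D association from ethnic differences that arise in other ways. A pooled slope without ethnicity cannot do that. The Implications section intends the results to inform food fortification strategies and a later randomized trial, so a between-group artefact could be carried forward.

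**Working it through.** **1. Where f = 0.25 comes from.** The plan's sample size is for the ethnic-group comparison: three groups, five time points, f = 0.25, 80% power, 5% level. The correlation between time points is not stated in the article; 0.5 is assumed here.

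- Noncentrality = f² × N × m / (1 + (m − 1)ρ) = 0.0625 × 96 × 5 / (1 + 4 × 0.5) = 10, with 2 and 93 degrees of freedom.
- Power = 0.802, and 96 is the smallest balanced total that reaches 80%. The stated 32 per group reproduces.

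So f = 0.25 is the ethnic difference the plan itself works with.

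**2. Ethnic gaps in 25(OH)D (assumption).** The stated deficiency rates (White 17.5%, AC 33%, SA 50%) are converted on a normal scale with a common SD. Group means above the deficiency threshold are 0.93, 0.44 and 0 within-group SD. Their mean is 0.458, and the between-group variance is (0.476² + 0.018² + 0.458²) / 3 = 0.146.

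**3. Pooled slope when the true within-group slope is zero.**

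Slope = between-group covariance of response and 25(OH)D / (1 + between-group variance of 25(OH)D), in within-group SD units.

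For White < AC < SA in equal steps at f = 0.25, the response means are −0.306, 0 and +0.306. The covariance is −0.306 × (0.476 + 0.458) / 3 = −0.095, and the slope is −0.095 / 1.146 = −0.083.

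**4. False-positive rate.** 4,000 simulated trials per scenario, 32 per group, zero within-group slope, two-sided 5%. The four planned covariates are simulated as unrelated to ethnicity, exposure and outcome. At f = 0.25:

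| Assumed response pattern | Expected pooled slope | Rejects, ethnicity omitted | Rejects, ethnicity included |
|---|---|---|---|
| White < AC < SA | −0.083 | 13.2% | 5.4% |
| White < AC = SA | −0.074 | 10.0% | 4.4% |
| Only SA higher | −0.071 | 10.5% | 3.9% |
| Only AC higher | −0.003 | 5.5% | 5.9% |

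The model with ethnicity is correctly specified here, so its true rate is 5% and the scatter in the last column is simulation error.

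Hand check of the first row: the pooled residual variance is 1 + 0.0625 − 0.083² × 1.146 ≈ 1.055. The expected t is 0.083 × √(96 × 1.146 / 1.055) ≈ 0.85, and the normal probability beyond ±1.96 is about 13.6%, in line with 13.2%.

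**5. Range over f**, for the first three patterns: about 6% at f = 0.10, 15–18% at f = 0.32 and 20–24% at f = 0.40. The value 0.32 is 0.25 × √(5/3), the equivalent for an average of five readings correlated at 0.5.

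**6. Strength of the within-group regressions.** The smallest partial correlation detectable with 80% power is about 0.46 with 32 people and about 0.28 with 96. The latter is unchanged when the two ethnicity indicators are added.

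**The case against.** Several points on the other side have weight.

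- **The pooled fit is one of two.** The same sentence plans regressions within each ethnic group. These match the wording of the primary outcome at least as well as the pooled fit and carry no between-group confounding. A reader might infer that the pooled regression is the primary analysis; the protocol does not say so. This limits the flaw to one fit. It does not remove it, because a significant pooled slope beside three weak, non-significant ones is a likely result and the article does not say which governs.
- **Bias is not inevitable.** A reader might infer that ethnic differences are bound to appear as a vitamin D effect. That needs response differences that do not run through vitamin D, survive adjustment for BMI and body fat, and follow the ordering of 25(OH)D. The protocol gives a response figure for South Asians against Whites only. If only African-Caribbeans differ, the bias is close to nil.
- **The size is not a protocol figure.** The deficiency rates are UK-wide. The Introduction cites 80–97% deficiency in Tower Hamlets, so the gaps in this sample may be smaller. The protocol relates BMI to ethnicity, and BMI and body fat to 25(OH)D and glycemic response; adjusting for them may absorb part of the confounding, which the simulation did not test. The reported two- to threefold peak cannot be turned into f without an SD, so it does not justify much larger error rates.
- **Vitamin D may carry part of the ethnic difference.** In that case some of the between-group contrast is not spurious. That stands, but the pooled model cannot tell this case from confounding.

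A reader might also infer that fasting glucose must be added, since the ANCOVA of the same outcomes adjusts for "confounding factors including fasting glucose concentration, age, sex, BMI, and body fat percentage". The documents do not support this. The iAUC already counts only area above fasting, and the Introduction cites evidence that vitamin D supplementation may lower fasting glucose in patients with type 2 diabetes. Fasting glucose may thus lie on the pathway of interest, and the regression has a different exposure from the ANCOVA.

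**Conclusion.** The concern holds for the all-participant regression. Its stated covariates omit a variable that the protocol itself relates to both exposure and outcome, so ethnic differences can appear there as a vitamin D association.

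At the plan's own f = 0.25 the effect is moderate: a spurious slope of about −0.07 to −0.08 SD per SD and a false-positive rate of about 10–13% when South Asians, or South Asians and African-Caribbeans, have the higher response, against about 5% when only African-Caribbeans differ. These figures assume UK deficiency gaps on a normal scale, no within-group association, and BMI and body fat unrelated to ethnicity. The case for changing the model rests on the omission, not on the exact percentages. The within-group regressions are sound on this point but too weak to settle what the pooled fit leaves open.

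**What to change.** In the Data analysis section, and in the abstract's summary of the model, state something to this effect: *The all-participant models for iAUC and peak value include ethnic group as two indicator variables together with age, gender, body fat and BMI. The within-group models are kept. The pooled model without ethnic group is reported as a sensitivity analysis only.*

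The cost is two degrees of freedom and some precision. Removing the between-group variation in 25(OH)D raises the standard error of the slope by at most √1.146 ≈ 1.07 times under the gaps assumed above. At f = 0.25 the rise is about √(1.146 / 1.055) ≈ 1.04 times, because ethnicity also reduces residual variance. The precision given up comes from the confounded contrast. The sample size does not change, and no new data are needed because ethnicity is already collected.

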The postprandial glycemic response (PGR) has important implications for the development of T2DM (Shibib et al., 2024). The oral glucose tolerance test (OGTT) is widely used to assess insulin sensitivity and pancreatic β-cell function and to assess an individual's metabolic capacity to handle carbohydrate-containing foods (American Diabetes Association, 2013). However, a recently published study indicated that within-subject variations in the PGR pattern may exist between OGTT and food intake, suggesting the necessity of combining OGTT and a meal/drink tolerance test for individualized glycemic management (Liu et al., 2022). There is poor awareness about vitD and its impact on health in the UK. Although the COVID-19 pandemic has brought increased public attention to vitD, only around one in six individuals in the UK have been reported to take a daily vitD supplement (Gov.uk, 2022b). However, no such data is currently available for ethnic minority groups or residents of East London. We are also interested in dietary vitD intake between different ethnic groups in East London, which will partly explain the vitD status of the target population.

Overall, the evidence on the association of vitD and the risk factors of T2DM in the ethnic minority groups is scant. There is an urgent call for research on ethnic minority populations to address health inequality (The NHS Race and Health Observatory, 2021). This proposal aims to respond to the above call by focusing on ethnic minority communities in East London via investigating the association between vitD status and PGRs among White Caucasian, SA, and AC adults. The objectives of the study include (1) investigating PGRs to an OGTT, as well as to the consumption of a commonly consumed drink, pure orange juice (OJ); (2) measuring parameters in the blood including 25(OH)D (an indicator of vitD status), and other relevant tests including calcium, parathyroid hormone (PTH), blood lipid profile, inflammatory parameters; (3) assessing the knowledge and perception of vitD; (4) evaluating the dietary vitD intake, in White Caucasian, SA and AC adults.

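### Separate per-drink ANCOVAs and a Pearson correlation cannot show whether responses, or ethnic differences in them, differ between the two drinks

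*Protocol article*

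**What the plan says.** The Introduction justifies a second drink on the ground that "within-subject variations in the PGR pattern may exist between OGTT and food intake". The first objective is stated there as "investigating PGRs to an OGTT, as well as to the consumption of a commonly consumed drink, pure orange juice (OJ" (the short form for the juice), and the objectives cover the three ethnic groups. The Method section describes a randomised crossover with repeated measures, so each participant supplies both responses.

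Under Outcome measures, the primary outcome is the association of plasma 25(OH)D with iAUC and peak value. Ethnic differences in iAUC and peak value are secondary outcomes.

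Under Data analysis, iAUCs and peak values "between ethnic groups after each drink consumption will be analyzed by one-way ANCOVA", adjusted for fasting glucose, age, sex, BMI and body fat percentage. One analysis connects the drinks: a Pearson correlation of iAUCs and of peak values, whose declared purpose is to identify how the response pattern differs between drinks. No term or test for ethnicity by drink is stated. P-values are to be reported with 95% confidence intervals.

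**The concern.** The article names an analysis for the difference between drinks, and that analysis does not answer the question. A Pearson correlation measures linear agreement. It is unchanged if every response to one drink is shifted by a constant or multiplied by a positive factor, and it has no ethnicity term.

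The per-drink ANCOVAs answer a different question, namely whether the groups differ after this drink. Side by side they give two results, and no analysis says whether the ethnic differences are alike. If one is significant and the other is not, a reader may take that as a drink-specific ethnic difference, although a difference in significance is not a test of a difference. The crossover supplies the within-person pairing that a proper test needs, and the stated plan uses it only for the correlation.

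**Working it through.** **Inputs from the protocol article (Data analysis).** "This study aims to achieve an effect size of 0.25 in the PGRs among three ethnic groups"; five time points; "to achieve 80% power in the study"; "at the 5% level of significance"; 32 per group, 96 in total, 106 with 10% dropout; method "based on F-tests for ANOVA: repeated measures, between-subjects factors". **Assumed, because the text shown does not give them:** the correlation between time points (0.5) and the correlation r between a person's two drink responses (0.3 to 0.7, with wider values shown).

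**1. The plan's own figure.** For the between-subjects factor, λ = f²·N·m / (1 + (m − 1)ρ) = 0.0625 × 96 × 5 / (1 + 4 × 0.5) = 10.0, with 2 and 93 df. Power is 0.802, so 96 reproduces. 96 × 1.1 = 105.6, which gives 106.

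**2. Power of one planned ANCOVA.** Each person now contributes one summary value per drink. λ = f²·N = 0.0625 × 96 = 6.0, with 2 and 96 − 3 − 5 = 88 df (five covariates). Power is 0.57 at N = 96 and 0.62 at N = 106. For 80% power the summary value would need f = 0.25 × √(5/3) = 0.323.

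**3. Chance that exactly one drink is significant when the true standardised effect is the same for both.** Simulation, 100,000 trials per setting, 3 × 32, bivariate normal responses, five covariates:

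| Effect on each summary value | Power per drink | r = 0.3 | r = 0.5 | r = 0.7 |
|---|---|---|---|---|
| f = 0 (no ethnic effect) | 5% | 9% | 8% | 7% |
| f = 0.25 | 57% | 41% | 34% | 26% |
| f = 0.323 | 80% | 27% | 23% | 18% |
| f = 0.4 | 94% | 10% | 9% | 7% |

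Closed-form check at r = 0, f = 0.25: 2 × 0.569 × 0.431 = 0.49, and the simulation gives 49%. At r = 0.9 and f = 0.25 it is 15%. Over all settings run the range is about 4% to 49%.

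**4. What a direct test does.** Comparing ethnic groups on the within-person drink difference at the 5% level rejects in 5% of trials when the ethnic differences are equal on the scale analysed.

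**5. The scale matters.** The loads are 75 g glucose and 30 g sugar (Study design), a ratio of 0.4. Suppose, as an assumption, that the juice response is simply 0.4 times as large in mean differences and in SD. The difference score then has effect 0.6 × 0.25 = 0.15 and SD √(1 + 0.16 − 0.8r), which is 0.959 at r = 0.3 and 0.775 at r = 0.7. The standardised effects are 0.156 and 0.194, and the raw-scale interaction test rejects in 25% and 37% of trials although the ethnic effect is merely proportional. After standardising within drink the rate returns to 5%.

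**6. Power of the interaction test.** If the ethnic effect were f = 0.25 for one drink and zero for the other, with responses standardised within drink, the difference score has f = 0.25 / √(2(1 − r)) = 0.211, 0.25 and 0.323 at r = 0.3, 0.5 and 0.7. Power is 43%, 57% and 80%. Smaller departures would have less.

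**The case against.** The strongest case against is that nobody has promised a drink-specific ethnic difference. The aim and the outcomes concern ethnic differences in response and their link with vitamin D. The first objective asks for responses to each drink, and for that a per-drink ANCOVA is a legitimate analysis. The reason given for two drinks is agreement within a person, not effect modification by ethnicity. The ethnic comparison is a secondary outcome, 95% confidence intervals will accompany the P-values, and a fuller analysis plan that is not shown may hold an interaction test.

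Most of this stands. A reader might infer that the trial will read one significant and one non-significant result as a drink-specific ethnic difference, and will do so wrongly in 26–41% of cases. The documents do not support that. The article nowhere states such an inference. The percentages count how often the discordant pattern arises, not how often a conclusion is drawn from it. They also apply the plan's f = 0.25, which belongs to a five-time-point calculation, to a single summary value, with equal effects and an assumed r.

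The appeal to an unseen plan does not settle the matter. The article does fix a method for finding a difference in pattern between drinks, and that method is unsuitable for the purpose. Separate confidence intervals help a reader but do not compare the drinks formally.

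**Conclusion.** The point holds in a limited form. The per-drink ANCOVAs are valid for the stated ethnic comparison after each drink. What the article fixes badly is the link between drinks: a correlation cannot show whether responses, or ethnic differences in them, differ between glucose and juice, and two separate tests cannot support a drink-specific ethnic difference.

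The 26–41% rests on equal standardised effects of f = 0.25 on the summary outcome, 32 per group, and an assumed r of 0.7–0.3. Under other plausible settings the discordant pattern is less common: 18–27% at 80% power per drink and 7–9% with no ethnic effect. The per-drink analyses and the primary outcome are not invalidated.

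**What to change.** Keep the per-drink estimates, and keep the correlation as a description of agreement between drinks. For iAUC and for peak value, add one linear mixed model with ethnicity, drink, ethnicity by drink, visit and the planned covariates. Use an unstructured within-person covariance so that variances may differ by drink.

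Pre-specify a single scale before the data are analysed. Responses standardised within drink are one workable choice. A log or ratio scale may fail, because only area above fasting is counted and iAUC can be near zero. State that any claim of a drink-specific ethnic difference will rest only on the interaction estimate with its 95% confidence interval, as a secondary analysis.

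The cost is analysis wording. The model can be fitted in the named software and needs no new data. The drawbacks are limited interaction power, so that no evidence of a difference between drinks may be the usual result, and a conclusion that depends on the scale chosen.

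### The between-drink correlation names no ethnic group, so as written it mixes ethnic mean differences with person-level association; the distortion is small at the planning effect but cheap to remove.

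*Protocol article*

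**What the plan says.** In the protocol article, Data analysis, the between-drink analysis is one sentence, which begins "The correlation of iAUCs and PVs between the two drink consumptions is analyzed by". The method named there is Pearson's, and the stated purpose is to show how the response pattern differs between drinks. It gives no grouping, stratum or covariate, and does not state whether participants are pooled.

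The neighbouring analyses are explicit. The regression of iAUC and peak value (PV) on 25(OH)D is adjusted for age, gender, BMI and body fat, and is run "including all participants, as well as in different ethnic groups". The ethnic comparison after each drink "will be analyzed by one-way ANCOVA adjusted by confounding factors including fasting glucose concentration, age, sex, BMI, and body fat percentage".

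The design expects the groups to differ. The sample size paragraph says "This study aims to achieve an effect size of 0.25 in the PGRs among three ethnic groups", and the Introduction says "Recent research revealed that the postprandial glucose peak in SAs is 2–3 times greater than in White Caucasians". The Introduction's reason for a second drink concerns individuals: it cites evidence that "within-subject variations in the PGR pattern may exist between OGTT and food intake" and links this to individualized glycemic management.

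**The concern.** A Pearson r over a sample made of three groups has two sources: how individuals vary together within their group, and how the group means line up across the two drinks. The ANCOVA already addresses the second. The reason given for using two drinks concerns the first.

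If one ethnic group is higher on both drinks, that shift alone makes r positive, even if one person's response to glucose says nothing about that person's response to juice. If the ethnic pattern differs between drinks, the pooled r understates the person-level association. In either case the single number does not answer the individual-level question.

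PV has a further source. If it is an absolute concentration, a person's habitual fasting level enters both visits and adds to r. iAUC is not affected in this way, because only area above fasting is counted.

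**Working it through.** **The plan's own figure.** Inputs from Data analysis: f = 0.25, three groups, five time points, 5% level, 80% power. The correlation among repeated measures is not in the article (details are in its Appendix 3); 0.5 is assumed. Then λ = f²·N·m/(1 + (m − 1)ρ) = 0.0625 × 96 × 5/3 = 10 with 2 and 93 df, which gives power 0.802. N = 96 is reproduced.

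**Pooled r when group means follow the same pattern on both drinks.** Let B be the ratio of between-group to within-group variance, B = f². Then pooled r = (r_within + B)/(1 + B).

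- f = 0.25: B = 0.0625. r_within 0 gives 0.0625/1.0625 = 0.06; 0.3 gives 0.3625/1.0625 = 0.34; 0.6 gives 0.6625/1.0625 = 0.62.
- The planning f refers to single time points. For a summary such as the mean of five points at ρ = 0.5, f becomes 0.25 × √(5/3) = 0.32 and B = 0.104. r_within 0 then gives 0.104/1.104 = 0.09.
- f = 0.5: 0.25/1.25 = 0.20. f = 1.0: 1/2 = 0.50.

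At n = 96, |r| must reach 0.201 for P ≤ 0.05. In simulation (32 per group, 20,000 runs, r_within = 0), the share of trials with P ≤ 0.05 was:

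| f on both drinks | Mean pooled r | P ≤ 0.05 |
|---|---|---|
| 0.25 | 0.06 | 8.5% |
| 0.32 | 0.09 | 15% |
| 0.5 | 0.20 | 51% |
| 1.0 | 0.50 | about 100% |

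With group means removed, mean r was 0.00 and about 5% were significant.

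**When the patterns differ.** With r_within = 0.6 and f = 0.32, pooled r falls to 0.6/√1.104 = 0.57 if only one drink shows an ethnic difference, and to (0.6 − 0.104)/1.104 = 0.45 if the patterns are opposite. Simulation gave 0.57 and 0.45.

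**If the Introduction's 2–3-fold difference applied to the incremental response to both drinks.** The CVs and the African-Caribbean mean are assumptions. For a 2-fold South Asian mean with African-Caribbean equal to White (means 1, 2, 1), the between-group variance is 0.222.

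- CV 40%, constant SD: B = 0.222/0.16 = 1.39, r = 0.58.
- CV 60%, SD proportional to the mean: within-group variance = 0.36 × (1 + 4 + 1)/3 = 0.72, B = 0.31, r = 0.24.

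Across 2- and 3-fold ratios, CV 30% to 70%, proportional SD, and African-Caribbean equal to either White or South Asian, simulation with r_within = 0 gave pooled r of 0.13 to 0.73 and P ≤ 0.05 in 26% to 100% of trials.

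**Shared fasting level in absolute PV.** r = s_F²/√((s_F² + s_O²)(s_F² + s_J²)), where F is fasting, O the glucose drink and J the juice. Assumed SDs in mmol/L:

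- s_F 0.3, s_O 1.5, s_J 0.9: 0.09/√(2.34 × 0.90) = 0.06.
- s_F 0.5, s_O 1.2, s_J 0.7: 0.25/√(1.69 × 0.74) = 0.22.

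**Precision on Fisher's z scale (95% half-width, 32 per group).**

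- Pooled r: 1.96/√93 = 0.203.
- Partial correlation on group: 1.96/√91 = 0.205, about 1% wider.
- Three group r values combined: 1.96/√(3 × 29) = 0.210, about 3% wider.
- Combined, with fasting glucose, age, sex, BMI and body fat also partialled out in each group: 1.96/√(3 × 24) = 0.231, about 14% wider.

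**The case against.** The strongest reply is that the effect is negligible where the trial plans to be. At f = 0.25 an r of 0.06 is far below the 0.20 needed for significance, and a true r of 0.3 to 0.6 moves by only 0.02 to 0.04. Zero association between one person's responses to two sugary drinks is also an extreme case. This stands, and it limits the finding.

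A reader might infer that pooling is bound to inflate r and will make the drinks look concordant when individuals' responses are unrelated. The documents do not support that. Inflation requires the groups to be ordered alike on both drinks, and the large values require carrying the Introduction's peak ratio, reported for identical carbohydrate loads, over to two drinks with 75 g glucose and 30 g sugar, with assumed CVs.

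The article is also silent rather than explicit about pooling, and a fuller plan may give by-group correlations. That is fair. But the method is stated, and the adjacent sentences name their adjustment or stratification, so a single unadjusted r is the plain reading.

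The correlation is not listed under Outcome measures, and no decision rests on it. An all-participant r is also a legitimate description of this sample, and the all-participant 25(OH)D regression does not adjust for ethnicity either. These points argue for keeping the pooled r, not for using it alone to answer a person-level question.

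**Conclusion.** The concern holds in a limited form. As written, the between-drink correlation is a pooled r that mixes ethnic mean differences with person-level association, and it can err in either direction. At the planning effect, with the same ethnic pattern on both drinks and no within-group association, expected r is about 0.06 to 0.09 and the false-positive rate about 8.5% to 15%. Distortion becomes serious only at around f = 0.5 or more on both drinks. The separate PV contribution of 0.06 to 0.22 depends on PV being an absolute concentration, on a fasting level common to both visits, and on the assumed SDs. This is an inexpensive improvement to a supporting analysis; it does not touch the primary outcome.

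**What to change.** In Data analysis, add to the correlation sentence that the association between drinks will also be estimated adjusted for ethnic group, with a 95% CI, and that the person-level interpretation rests on this estimate. Either of two methods serves:

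- a partial correlation on group; or
- within-group r values combined by Fisher's z, with the three group values shown, since one combined r presumes a similar correlation in each group.

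The second is safer if spread rises with the mean. With SD proportional to the mean and r_within = 0, the partial correlation rejected in about 7% to 17% of simulated trials, against 5.1% to 5.2% for the Fisher's z combination (CV 50%).

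State whether PV is an absolute concentration. If it is, remove fasting glucose or use peak minus fasting. The pooled r may still be reported, labelled as including between-ethnic differences.

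The cost is a sentence or two and a CI up to about 3% wider for group adjustment alone. Partialling out age, sex, BMI and body fat as well is optional; within groups of 32, together with fasting glucose, it brings the widening to about 14%.
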